## Abstract

**Background:**

Obesity and depression are two prevalent conditions that are costly to individuals and society. The bidirectional association of obesity with depression, in which unhealthy dietary patterns may play an important role, has been well established. Few experimental studies have been conducted to investigate whether supplementing specific nutrients or improving diet and food-related behaviors can prevent depression in overweight persons.

**Method/Design:**

The MooDFOOD prevention trial examines the feasibility and effectiveness of two different nutritional strategies [multi-nutrient supplementation and food-related behavioral change therapy (FBC)] to prevent depression in individuals who are overweight and have elevated depressive symptoms but who are not currently or in the last 6 months meeting criteria for an episode of major depressive disorder (MDD). The randomized controlled prevention trial has a two-by-two factorial design: participants are randomized to daily multi-nutrient supplement (omega-3 fatty acids, calcium, selenium, B-11 vitamin and D-3 vitamin) versus placebo, and/or FBC therapy sessions versus usual care. Interventions last 12 months. In total 1000 participants aged 18–75 years with body mass index between 25–40 kg/m^2^ and with a Patient Health Questionnaire-9 score ≥ 5 will be recruited at four study sites in four European countries. Baseline and follow-up assessments take place at 0, 3, 6, and 12 months. Primary endpoint is the onset of an episode of MDD, assessed according to DSM-IV based criteria using the MINI 5.0 interview. Depressive symptoms, anxiety, food and eating behavior, physical activity and health related quality of life are secondary outcomes. During the intervention, compliance, adverse events and potentially mediating variables are carefully monitored.

**Discussion:**

The trial aims to provide a better understanding of the causal role of specific nutrients, overall diet, and food-related behavior change with respect to the incidence of MDD episodes. This knowledge will be used to develop and disseminate innovative evidence-based, feasible, and effective nutritional public health strategies for the prevention of clinical depression.

**Trial registration:**

ClinicalTrials.gov. Number of identification: NCT02529423. August 2015.

**Electronic supplementary material:**

The online version of this article (doi:10.1186/s12888-016-0900-z) contains supplementary material, which is available to authorized users.

## Background

Depression and obesity are common conditions that have been consistently associated. Evidence-based research from epidemiological and clinical trials suggests a bidirectional link between being overweight and psychological health. Community-based cross-sectional studies found that depression is associated with an 18 % increased odds of being obese [17]. Longitudinal studies revealed that obesity at baseline increases the risk for onset of depression at follow-up by 55 %, and that depression at baseline increases the risk for onset of obesity at follow-up by 58 % [42].

One potential mechanism linking depression and obesity is an unhealthy diet. Consumption of processed foods such as fried foods, refined grains, and refined sugars is associated with both depression and obesity, while eating a more traditional healthy Mediterranean-style diet rich in fruits, vegetables, legumes, olive oil, fish and whole grains is associated with reduced depression [1, 11, 32, 53, 55, 56, 66–69]. These findings have also been observed in people with diabetes [18] and in older people [12]. These findings may suggest that more unhealthy food-related behavior is linked to mood states. Environmental, mood-related and food-related cues like emotions, distraction, food exposure or cooking skills can all influence the dietary intake of individuals. Empowerment to cope with these cues has been associated with positive mental health [44]. Because associations between affective states and eating behaviors have been found, frequent adherence to food-related behavior guidelines can result in a more healthy and regular dietary daily routine, higher ability to self-regulate dietary intake and increasing engagement with food as a positive activity [58].

In addition to effects of whole diet patterns, observational as well as meta-analytic evidence suggest that some specific nutrients, especially omega-3 fatty acids, folic acid, vitamin D3, selenium and calcium could have impact on depression as well [46, 49, 50, 65]. Several systematic reviews [4, 22, 41, 71] but not all [10, 54] suggest that omega-3 fatty acids may be effective at reducing depression or depressive symptomatology. A recent meta-analysis suggests that doses in the range 0.6–4.4 g of eicosapentaenoic acid (EPA) plus 0.2–2.2 g of docosahexaenoic acid (DHA) might be efficacious relative to placebo in reducing depressive symptoms in patients with depression [28]. Individuals with lower intakes of vitamin B were found to be more likely to be diagnosed with depression and to experience recurrent depressive episodes [5, 76]. Higher intakes of vitamin B6 in women and higher intakes of B12 among men were found to reduce major depressive disorder (MDD) risk [27]. Low levels of vitamin D were found in people with depression compared with controls [2, 46], in people with higher depression scores [30, 47], and were associated with higher depressive symptoms especially in persons with a previous history of depression [29]. In a male only sample, Black et al. [9] found an inverse association between serum 25-hydroxyvitamin D concentrations and symptoms of depression. Several trials have also found that vitamin D supplementation improves mood scores [40] and reduces depressive symptoms in obese people [33]. However, other controlled trials have found no benefit of supplementation on depressive symptoms in the general population [8, 19, 37]. Depression was significantly associated with low selenium blood levels [23, 26, 31] and low levels of dietary selenium were also associated with an increased risk for major depressive disorder [60]. Low dietary calcium was associated with self-rated depression in middle-aged women [6]. High intake of yogurt and calcium was associated with a lower prevalence of depressive symptoms during pregnancy in a cross-sectional study [48] and dietary intake of calcium was also associated with lower prevalence of depressive symptoms in workers [45].

The well-established epidemiological relationships between diet and depression and the positive results of several intervention studies raise the possibility that diet and nutrition may offer key modifiable targets for the prevention of MDD [56, 70]. Prevention can help to lessen the global burden of the depressive disease [16], and cost-effective interventions are required. Dietary and food related behavior interventions are potentially desirable, effective, pragmatic, scalable, and non-stigmatizing public health prevention strategies for depression. However, to date, few studies have directly manipulated diet and food-related behavior alone to examine their effects on preventing depression, leaving unresolved whether a true causal association exists from diet to depression [61] and none thus far have specifically targeted high-risk, overweight individuals.

Interventions focusing on changing food-related behaviors and shifting habitual eating patterns are one way to change diet and to have an influence on the onset of depressive episodes. Behavioral interventions can act as a selective prevention method targeting individuals or groups that are at higher risk of developing depression. An uncontrolled case series indicated the potential value of combining Behavioral Activation (BA) [43] with brief nutrition counselling among individuals with co-morbid MDD and obesity to both reduce weight and symptoms of depression [59]. BA focuses on increasing positive activities, reducing avoidance, and building routines and healthy behaviors to reduce depression. BA is an evidence-based psychological approach for depression which has demonstrated to be an effective intervention for depression in RCTs [15]. It includes detailed analysis of the antecedents and consequences of behavior in order to effectively change habitual behaviors, making it amenable to support the adoption of a healthy Mediterranean-style diet and food-related behavior. However, to date, combining BA with nutritional goals has not been tested in a controlled trial or applied to the prevention of depression.

Long-term depression prevention trials focusing on foods, nutrients and food-related behavior are currently lacking. Furthermore, studies have not fully delineated the relative influence of whole diet versus specific nutrient change on depression outcomes. Such studies are essential to determine whether it is feasible and effective to change food intake, specific nutrient intake, and/or food-related behavior for the prevention of depression. To address the gaps in the literature identified above, the Multi-country cOllaborative project on the role of Diet, Food-related behavior, and Obesity in the prevention of Depression (MooDFOOD) prevention trial will be conducted.

### Objective

The primary objective of the MooDFOOD prevention trial is to examine the feasibility and effectiveness of two different nutritional strategies to prevent a new episode of MDD in high-risk overweight persons with subsyndromal symptoms of depression. A secondary objective is to examine potential mediators and moderators of the beneficial effects (if any) of these nutritional strategies.

## Methods

### Study design

A 2 × 2 factorial randomized controlled prevention trial will be conducted to compare two nutritional strategies: a multi-nutrient supplement and a food-related behavioral change (FBC) intervention. A total of four intervention groups will be created: (1) placebo supplement group; (2) placebo supplement + FBC group; (3) multi-nutrient supplementation group; (4) multi-nutrient supplementation + FBC group.

### Recruitment and study settings

One thousand subjects will be recruited at four study sites in four different European countries (The Netherlands: GGZ inGeest and Vrije Universiteit Amsterdam, Amsterdam; United Kingdom: University of Exeter; Germany: University of Leipzig, Spain: University of Balearic Islands, with 250 subjects recruited per site) (see Fig. 1 for recruitment process).

**Fig. 1 Fig1:**
[figure not shown]
MoodFood participants flow-chart

The recruitment strategy includes websites; local advertisements in social media; mailings to registered subjects in the general practice setting or in other registers (e.g. city registers); invitation letters, MooDFOOD brochures and posters in public areas, articles in local newspapers, press releases to the national press as well as recruitment via other studies and trials conducted at the four sites.

### Eligibility criteria

Inclusion criteria for the study are that participants will be adults aged 18 to 75 years old, meet criteria for being overweight or obese (body mass index (BMI) between 25–40 kg/m^2^) and report subsyndromal symptoms of depression as operationalized by a Patient Health Questionnaire (PHQ-9) score of at least 5. Overweight individuals with elevated symptoms of depression will be recruited because both of these variables increase vulnerability for subsequent MDD episodes. This will increase the potential base rate of incidence of depression during the follow-up period, and, thereby, the sensitivity of the prevention study. Furthermore, a nutritional intervention has greater scope to be beneficial in this group, as both obesity and depression are associated with unhealthy diet and unhealthy food-related behaviors.

Because this is a prevention trial, rather than an acute treatment trial, participants will be excluded at baseline if presenting with a current episode of (including the past 6 months) MDD (according to psychiatric DSM-IV criteria), as determined in a structured MINI International Neuropsychiatric Interview 5.0 (MINI 5.0). Other exclusion criteria include: Current (in past 6 months) use of antidepressant drugs or psychological interventions; Current eating disorder; History of psychosis, bipolar disorder, substance dependence or other severe, psychiatric disorder that requires specialized clinical attention; History of or planned bariatric surgery; Currently pregnant or breastfeeding; Current severe, life-threatening physical disease (assessed using self-report); Severe cognitive impairment sufficient to limit the conduct of the study as assessed through research staff evaluation of participant’s ability to complete the screening instruments in an adequate manner; Currently adhering to supervised behavioral interventions that interfere with MooDFOOD prevention trial interventions; Unwilling to stop using specific dietary supplements that are used or are competing with the MooDFOOD prevention trial multi-nutrient intervention.

### Screening

Participants who are interested in the study are directed to the online screening tool on our study website [http://www.moodfood-vu.eu], which provides further information and includes questionnaires to assess key eligibility criteria such as age, BMI and depressive symptoms (PHQ-9). Those individuals who pass the screening phase and indicate an interest in the study will be contacted for a more detailed telephone interview to further explain the study and confirm eligibility.

The telephone interview consists of brief screening questions on mental and physical health to check the eligibility for the trial (see Table 1). The researcher will provide the applicant with an overview of the trial and conduct the MDD section of the MINI clinical interview to assess whether individuals meet the exclusion criterion for MDD (current or in the past 6 months). Applicants who satisfy the eligibility criteria will be informed about the study design and enrolled in the prevention trial. Where applicants cannot participate because they have a psychiatric disorder, they will be advised to discuss this with their General Practitioner, and contact details of organisations for further support are offered if appropriate. Additionally, any suicidal risk reported during the interview is assessed using a well-established protocol to ensure that appropriate clinical support is provided.

**Table 1 Tab1:** Inclusion and exclusion criteria of the MooDFOOD prevention trial

Inclusion criteria	
18 to 75 years old	
Body mass index between 25–40 kg/m^2^	
A PHQ-9 score of at least 5.	
Exclusion criteria	
Current (including the past 6 months) Major depressive Disorder (DSM-IV criteria, M.I.N.I. 5.0 interview).	
Current (in past 6 months) use of antidepressant drugs or psychological interventions	
Current eating disorder	
History of psychosis, bipolar disorder, substance dependence or other severe psychiatric disorder	
History of or planned bariatric surgery	
Currently pregnant or breastfeeding	
Current severe, life-threatening physical disease	
Severe cognitive impairment	
Currently adhering to supervised behavioral interventions that intervene with MooDFOOD interventions	
Unwilling to stop using specific dietary supplements competing with the MooDFOOD multi-nutrient intervention.	

*Notes*: *PHQ-9* patient health questionnaire, *MINI-5.0* MINI International Neuropsychiatric Interview 5.0

### Consent procedure, baseline and follow-up assessments

All eligible participants will then be invited to visit the research center for a face-to-face baseline assessment. The assessment takes place after written informed consent is provided, and consists of the Depression section of the MINI 5.0 to assess lifetime history of depression and a detailed interview, physical measurements (height, weight, waist circumference, blood pressure) and provision of self-administered questionnaires (see outcome measures and Table 2).

**Table 2 Tab2:** Measurements and Endpoints of the MooDFOOD prevention trial

			Follow-up (in months)			
Interview		Baseline	3	6	9	12
Informed Consent		✓				
Socio-demographics	Sex, Date of Birth, civil status, housing, education, job, income	✓				
MINI (V5.0)-Present MDE	Assessment of MDE according to the definitions/criteria of DSM-IV	✓	✓	✓		✓
MINI (V5.0)-Lifetime MDE	Historical assessment of MDE according to the definitions/criteria of DSM-IV	✓				
Depression history of family	Medical records	✓				
Chronic Illness	History of Chronic illnesses	✓				
Chronic Illness follow up	Has there been a change in health?		✓	✓		✓
Medication/supplement use	Medications and supplements used in last months	✓		✓		✓
Smoking	Smoking status	✓		✓		✓
Alcohol Use Disorders Identification test (AUDIT)	Alcohol disorders	✓				✓
Compliance	Morisky Adherence Scale		✓	✓	✓	✓
Physical Measurements						
Blood pressure		✓	✓	✓		✓
Anthropometrics	Weight, height, waist circumference	✓	✓	✓		✓
Blood collection	Multi-nutrient adherence, Health indicators, markers of disease	✓		✓		✓
Self-administered questionnaires						
PHQ-9	Screening of mental health disorders	✓	✓	✓		✓
IDS-SR30	Depressive symptoms	✓	✓	✓		✓
GAD-7	Anxiety symptoms	✓	✓	✓		✓
Euro-Quol-5D-5 L	Health-realted quality of life	✓	✓	✓		✓
TEFQ-R18	Eating behavior: cognitive restraint, uncontrolled eating and emotional eating	✓	✓	✓		✓
The Stunkard figure rating scale	Body weight perception (body image and perceived body size)	✓	✓	✓		✓
SRBAI	Automaticity of good and bad health habits and Mediterranian diet	✓	✓	✓		✓
BADS	Behaviour functionality: activation avoidance/rumination, work/school impairement, and social impairement	✓	✓	✓		✓
SBQ	Sendentary behaviour	✓	✓	✓		✓
SQUASH	Physical activity	✓	✓	✓		✓
Food behaviour and Sutainability	Meal pattern, practices, cooking and shopping, mindful eating, sustainability	✓	✓	✓		✓
FFQ-GA2LEN	Food frequency questionnaire measuring food intake	✓	✓	✓		✓

*Notes*: *MINI-5.0* MINI International Neuropsychiatric Interview 5.0, *PHQ-9* patient health questionnaire, *IDS-SR30* inventory of depressive symptoms self-rated, *GAD-7* generalized anxiety disorder-7, *Euro-Quol-5D-5 L* EuroQol instrument EQ-5D-5 L, *TEFQ-R18* three-factor eating questionnaire, *SRBAI* self-report behavioral automaticity index, *BADS* behavioral activation for depression scale, *SBQ* sedentary behavior questionnaire, *SQUASH* short questionnaire to assess health-enhancing physical activity, *FFQ-GA2LEN* food frequency questionnaire

After the baseline measurement, the participant will be randomised to one of the four intervention groups. Participants are given their first 3-month supply of pills (multi-nutrient supplement or placebo) with oral and written instructions on how to use them. Participants randomized to FBC will receive a telephone call from the behavioral therapist within one week for an appointment. Two weeks after randomization all participants will receive a telephone call to monitor the progression with supplements and to improve compliance.

All interventions will last 12 months. Follow-up assessment will be conducted by researchers unaware of the randomization status at 3, 6, and 12 months. Table 2 gives an overview of all measurements. Adherence to the supplement use will be measured at 3, 6, 9, and 12 months. In a subsample of trial participants (at least *n* = 50 per intervention arm) blood samples will be collected at baseline, at 6 and 12 months assessments for the investigation of nutrient concentrations to monitor multi-nutrient supplement compliance. Three-month supplies of pills will be provided at the 3, 6 and 9 month contacts.

### Randomization, allocation and masking

Participants will be randomized with equal probability (in a 1:1:1:1 ratio) to the four intervention arms. Permuted block randomisation will be employed using off-site blind computer generated quasi-random numbers obtained prior to trial commencement (https://www.sealedenvelope.com). Randomisation will be stratified according to recruitment site (four sites, enabling a steady flow to intervention groups) and participants’ history of depression status at the baseline assessment (lifetime history of MDD versus no MDD), determined by use of the MINI 5.0 interview for depression. The online randomization procedure will generate a unique code that is linked to both the multi-nutrient supplement (active nutrients or placebo) and FBC intervention status (yes/no).

Researchers will dispense the multi-nutrient supplements to the participant using the unique code. The placebo and supplement pills are identically packaged and indistinguishable from one another except through the unique codes. Therefore participants, therapists, and researchers will be blind (triple-blind) to supplement allocation. Participants of the FBC intervention will be contacted directly by the MooDFOOD therapist, thus ensuring that researchers, assessing the primary outcome, additionally remain blind (single-blind) to behavioral intervention status. All assessments will be conducted equally in all treatment conditions by researchers blind to randomization. To successfully maintain the blinding throughout the trial, the researchers conducting the patient assessments will be instructed to remind participants of the confidential nature of their treatment.

### Interventions

#### Multi-nutrient supplement

Participants will be asked to take the multi-nutrient supplements or placebo pills every day during one year. The placebo and multi-nutrient supplements will be plainly packaged and identical to one another in every way, with the exception of different codes on the packaging to enable blind allocation and unblinding if necessary.

The supplements will contain nutrients for which deficiency or low levels have been linked to depression risk in prior epidemiological or clinical intervention studies (see introduction). One daily supplement consists of omega 3 fatty acids in the form of 1412 mg of EPA and DHA (ratio 3:1) in a pharmaceutical form of a soft gelatine capsule of non-porcine origin with an enteric coat to prevent backflow. The other daily supplement is a multi-nutrient pill containing 100 mg of Calcium, 30 μg of Selenium, 400 μg of Folic acid (folate) and 20 μg of vitamin D3.

To match the active nutrient supplements, there will also be two placebo pills: a sunflower oil capsule with similar filling material and colour as the fatty acid capsule and a second pill with similar colour and shape as the multi-nutrient supplement containing Microcrystalline cellulose; Corn Starch; Polyvinylpyrrolidone; Crosslinked carboxymethylcellulose Sodium; Magnesium Stearate and Magnesium Silicate.

#### Food-related behavioral change (FBC)

The FBC intervention will consist of up to 21 sessions (up to 15 individual sessions of 30 min, provided in single or double (1 h) meetings; in addition to up to 6 group-based sessions lasting approximately 1 h). Individual sessions with the therapist will occur weekly at first and then every two weeks, and the final 6 sessions in groups of up to 10 people will take place monthly and then bimonthly. Different sessions may be delivered over the telephone or via web chat software such as Skype™. The treatment is manualized, with a handbook outlining the general principles of the intervention and mapping out the required content of each session. The intervention includes detailed analysis of each participant’s behavior to determine idiosyncratic triggers and functions of unhelpful (e.g., mood-related snacking) and helpful food-related behavior, in order to reinforce helpful behaviors and to implement effective alternatives to unhelpful behaviors, building on behavioral approaches proven effective in depression [15, 43]. The FBC intervention incorporates the standard approaches of BA including self-monitoring, functional analysis, and activity scheduling, with a focus on reducing avoidance and changing habits, with specific nutritional advice related to mood focused on building up a healthy Mediterranean style diet and improving food-related behaviors (e.g. regular meals per day) [39, 57]. At each site, clinicians familiar with behavioral activation principles (e.g., clinical psychologists, psychological wellbeing practitioners) will receive specific training in the FBC and on diet and food-related behavior by a nutritional scientist (IB) and will deliver the intervention. A dietician will be available for consultation across all sites.

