### Sample size

Effective preventive interventions in high-risk groups are found to reduce the onset of depression by as much as 25–50 % [7]. We have therefore powered this trial at the conservative end of this range, by assuming a difference of 33 % in the 12-month cumulative incidence rate of DSM-IV episodes of MDD between the presence of an active condition (estimated 12-month cumulative incidence of MDD 20 %) versus its absence (estimated 12-month cumulative incidence of MDD 30 %) (i.e., FBC versus no FBC; multinutrient supplement versus placebo). The 2×2 factorial design is efficient for sample size and power and enables us to test for potential synergistic interactions between interventions [13, 14]. Assuming a difference between an active condition (20 % incidence of MDD) and a control condition (30 % incidence of MDD), 392 participants would be needed to evaluate the main effect of each nutritional intervention assuming a 2-sided test at α = .05 and a power of (1 − β) = 0.90. This means that 196 participants in each of the four cells would be needed. Assuming a follow-up attrition rate of 22 %, a total of 250 participants per cell would be sufficient. A reduction in sample size to 147 participants in each cell would reduce the power to detect an effect of this magnitude to 80 % power.

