### Statistical analysis plan

Statistical reporting will follow the CONSORT standards [72]. Missing data will be inspected and handled via full information maximum likelihood (FIML) or multiple imputations (MI) as appropriate. The primary analyses will be Intention-To-Treat (ITT) analyses [78]. Subsequent analyses will use the Complier Average Causal Effect (CACE) analysis [3, 20] to provide an estimate of a treatment effect taking into account adherence and compliance with the treatment, whilst retaining the benefits of randomization.

Following the 2×2 factorial design of the trial, we will test for the effects of the two nutritional strategies separately as well as combined using logistic regression models for the dichotomous primary outcome (12-month cumulative incidence of episodes of major depressive disorder). The secondary outcomes will be examined using mixed models or generalized estimating equations (GEE) to assess the longitudinal change in depressive symptoms, and other secondary outcomes. We will adjust the analyses for site and history of MDD to account for the two stratification variables used in the randomization [34]. The results from the trial will be prepared as comparative summary statistics with 95 % confidence intervals. *P*-values <0.05 will be considered statistically significant.

For the secondary objectives, we will conduct mediation analyses to gain insight into mechanisms that could explain the potential effect of the nutritional interventions on depression. We will use modern causal inference methods using parametric regression models to assess mediation effects [21]. This involves using parametric regression models to test for mediation of the dietary interventions on depression through changes in the mediating variables. In addition, we will investigate potential moderation of the nutritional strategies on depression by site, age, sex, educational level, comorbid illness, initial BMI, and depression history.

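### FBC is delivered by shared therapists and partly in groups, but the sample size and the stated primary model treat participants as independent; if outcomes correlate within therapist or group, the FBC interval is too narrow and the 90% power is not met

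*Protocol article*

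**What the plan says.** All statements are in the Protocol article.

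- **Delivery** (Food-related behavioral change). Clinicians at each site deliver up to 15 individual sessions and up to 6 group sessions: "the final 6 sessions in groups of up to 10 people will take place monthly and then bimonthly". The number of therapists and their caseload are not given.
- **Sample size.** For 30% versus 20% incidence, a two-sided α of 0.05 and 90% power, the article states that "392 participants would be needed to evaluate the main effect of each nutritional intervention". This is then translated to cells: "196 participants in each of the four cells would be needed". On dropout: "Assuming a follow-up attrition rate of 22 %, a total of 250 participants per cell would be sufficient". The section contains no design effect, ICC or therapist number.
- **Primary analysis** (Statistical analysis plan). The 12-month cumulative incidence is analysed by logistic regression. On covariates: "We will adjust the analyses for site and history of MDD to account for the two stratification variables used in the randomization". Mixed models or GEE are named only for secondary outcomes, to describe change over time.

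**The concern.** Randomisation is by individual, but half of the participants are then treated by a limited number of therapists and later sit in groups together. The other half have no therapist and no group. This is a partially nested design: outcomes may be correlated in the FBC half only.

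A positive correlation inflates the variance of the FBC incidence. A model that assumes independence does not see this. Adjusting for site removes differences between sites, but differences between therapists or groups within a site remain.

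The FBC main effect is one of the two primary comparisons and is judged at P < 0.05. A borderline FBC result could therefore be declared significant only because clustering was ignored. The supplement contrast is largely protected, because active and placebo pills are randomised across the same therapists and groups.

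**Working it through.** **Inputs from the article.** Incidence 30% without and 20% with the intervention; two-sided α = 0.05; power 0.90; 392 per factor level (2 × 196); 22% attrition; 250 per cell; 250 participants per site with 1:1:1:1 allocation; groups of up to 10.

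**Inputs assumed, because the article gives neither.** ICC of 0.01 to 0.05; cluster size m of 10 (one therapy group) or 25 (one therapist's caseload). About 125 FBC participants are randomised per site (half of 250), so 25 per therapist means about 5 therapists per site.

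**Step 1: reproduce the stated sample size.** Independent two-proportion formula, pooled variance under the null, no continuity correction:

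n = [1.960 × √(2 × 0.25 × 0.75) + 1.282 × √(0.30 × 0.70 + 0.20 × 0.80)]² / 0.10² = 391.9, so 392 per level.

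At 80% power the same formula gives 293.2, so 294 per level = 2 × 147, the article's fallback figure. Both match exactly, so no allowance for clustering is hidden in them. There is no reserve either: 250 × 0.78 = 195 evaluable per cell against 196 needed.

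**Step 2: variance under partial nesting.** Only the FBC level is inflated, by DE = 1 + (m − 1) × ICC.

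**Step 3: type I error of the model that ignores clustering.** Under the null both levels have the same incidence, so the true variance is (1 + DE)/2 times the variance the model assumes:

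type I error = 2 × Φ(−1.96 / √[(1 + DE)/2])

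For m = 25, ICC 0.05: DE = 1 + 24 × 0.05 = 2.2; √1.6 = 1.265; 1.96/1.265 = 1.549; type I error = 12.1%.

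**Step 4: power of a test that accounts for clustering.** With 392 per level, SE = √[(0.21 + 0.16 × DE)/392].

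- Unpooled: power = Φ(0.10/SE − 1.96).
- Pooled null variance: power = Φ([0.10 − 1.96 × SE₀]/SE), with SE₀ = √[0.1875 × (1 + DE)/392].

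For m = 25, ICC 0.05: SE = 0.0379 and SE₀ = 0.0391, giving 75% (unpooled) and 73% (pooled).

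| Cluster size m | Assumed ICC | DE | Type I error, clustering ignored | Power, clustering accounted for |
|---|---|---|---|---|
| any | 0 | 1.00 | 5.0% | 90% |
| 10 | 0.01 | 1.09 | 5.5% | 89% |
| 10 | 0.05 | 1.45 | 7.7% | 84–85% |
| 25 | 0.02 | 1.48 | 7.8% | 83–84% |
| 25 | 0.05 | 2.20 | 12% | 73–75% |

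The last two columns describe different tests. The model that ignores clustering keeps more nominal power because it uses too small a standard error: at m = 25, ICC 0.05 it has 12% type I error and 85% power. The 73–75% belongs to a test with the correct standard error.

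**The case against.** **The analysis half rests partly on silence.** The article is condensed, and a separate statistical analysis plan may exist. The covariate sentence explains the stratification factors; it does not say that the list is complete or that the standard errors assume independence. This stands in part: a therapist or group term could be added there. It would not, however, make the 90% power claim for FBC correct, because that claim is already fixed here on an independence formula.

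**The size is assumed.** This stands. A reader might infer that the FBC interval and p-value are certainly too optimistic. The documents do not support that: with ICC 0 nothing changes, and with groups of 10 and ICC 0.01 the loss is about one point of power. Only the direction follows, and only for a positive correlation.

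**Clustering may be modest.** Up to 15 of the 21 sessions are individual and come first, and 10 is a maximum group size. MDD onset is counted from the 3-month interview onward, so onsets before the group phase cannot come from shared groups. Delivery is manualized, supervised, certified and fidelity-rated. These points are fair and argue for the lower end of the range. They do not show an ICC of zero, and sharing a therapist starts with the individual sessions.

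**The remedy has limits.** With few therapists, a random intercept on a binary outcome is poorly estimated. Conditioning on the trial's own therapists is also a defensible, though different, target of inference. The first point is why a small-sample correction is needed whichever method is used.

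**Conclusion.** The concern holds in conditional form. The sample size demonstrably assumes independence and has no reserve, and the stated primary model contains nothing for therapist or group. If outcomes correlate within therapist or group, the FBC interval is too narrow, its type I error is above 5% and a valid test falls short of 90% power. Under the assumed range this runs from nearly negligible (5.5%; 89%) to material (12%; 73–75%).

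Two further inferences should be resisted. The supplement comparison is not undermined. Nor does the calculation show that the trial is too small to be useful: with groups of 10 and ICC up to 0.05, valid power stays at 84% or more, above the 80% level that the article itself quotes. Confidence is high on the direction given a positive ICC and low on the size. Severity: should-fix.

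**What to change.** 1. Record a therapist identifier and a group identifier for every FBC participant during delivery. Recruitment was ongoing at publication, and these may be hard to reconstruct later.
2. Analyse the FBC effect with a partially nested logistic model (random intercept for therapist or group in FBC participants only), or with cluster-robust standard errors treating each participant without FBC as a cluster of one. Specify a small-sample correction in either case, because therapists may be few.
3. Use the same structure for the FBC effect on the secondary outcomes.
4. State the expected number of therapists and the group size, and restate FBC power over an assumed ICC range, as in the table above.

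The cost is two identifier variables and revised analysis wording. The downside is a somewhat wider FBC interval and a lower stated FBC power. No additional participants are required.
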